### Adverse events

All adverse events reported by participants or observed by therapists will be recorded and followed until they have abated or a stable situation has been reached.

### Data management

Each participant will be randomly assigned a personal identification code (ID), which will be used on all data. All data will be registered in a CASTOR EDC database by direct entry. The participant ID list will be stored with password protection and will only be accessible to the investigators. All files will be kept for 15 years in secure conditions.

### Sample size

We aim to achieve sufficient power to detect differences in both the short term (T1, primary endpoint) and longer term (T2). Because the expected change in VO_2peak_ is somewhat larger at T1, we used change in VO_2peak_ from T0 to T2 for the sample size calculation. Based on previous studies of exercise programmes in NMD, we expect a difference in change in VO_2peak_ from T0 to T2 between the intervention and control group of + 2.5 ml/min/kg (10%) [16, 53, 54].

Based on an effect size of 2.5 ml/min/kg, 1:1 group allocation, standard deviation of 4.7 ml/min/kg (based on previous studies) and a two sided α of 0.05, a sample size of *n* = 76 per group will be needed to obtain 90% power. However, because we will perform an Analysis of Covariance (ANCOVA), in which the baseline measurement will serve as covariate, a correction for the correlation between baseline and follow-up scores should be made [55]. In a previous RCT by our group, the correlation coefficient (r) was 0.71, resulting in *n* = 38 participants per group (76 x (1-r^2^)). As we expect a maximal drop-out rate of 15% based on previous studies [56, 57], 90 participants will be recruited (45 per group).

### Statistical analyses

Data collected in this study are all quantitative and therefore means, medians and percentages (as applicable) will be used as descriptive statistics. Data will be analysed with SPSS statistical software (IBM Corporation, Armonk, NY, USA), and *P* ≤ 0.05 used as significance level. We will perform analyses on intention-to-treat basis and include all randomized participants.

The primary outcome analysis compares the change from baseline to T1 (directly post-intervention) in VO_2peak_ between the groups based on ANCOVA, using the baseline value as covariate. Missing data will be imputed, first by interpolation if possible, and otherwise by multiple imputation. The secondary analysis compares the change from baseline to T2 (12 months follow-up) in VO_2peak_ between the groups based on ANCOVA, using the baseline value and stratification factors as covariates.

Additionally, we will evaluate between-group differences in secondary outcomes at the 6-, 12- and 18-month follow-up assessments (i.e. T1, T2 and T3 respectively), with linear mixed model analysis for repeated measurements. Random effects for the intercept and time will be included in the model. Baseline values, treatment group, time and a group by time interaction term will be included as covariates. In addition, a random effect for treatment centre will be included to account for partial clustering within centres. Multivariate linear regression analysis for longitudinal data will be used to investigate associations between participant and disease characteristics and effect of intervention.

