### Study population

The study population consists of individuals with slowly progressive NMD, focusing on prior poliomyelitis and Post-Polio Syndrome (PPS), Charcot-Marie-Tooth disease (CMT), and other slowly progressive NMD. Participants will be recruited from six participating hospitals and rehabilitation centres and through the nationwide patient organization for NMD ‘Dutch Association for Neuromuscular Diseases’. The participating centres are Amsterdam University Medical Center, location AMC (Amsterdam), University Medical Center Utrecht (Utrecht), Rehabilitation Center Klimmendaal (Arnhem), hospital Sint Maartenskliniek (Nijmegen) and Merem Medical Rehabilitation (Almere and Hilversum). Potentially eligible individuals will receive an information letter. Subsequently, during a phone call, current attitudes and beliefs about exercising in NMD, actual physical fitness and activity levels, and barriers and facilitators to physical activity will be discussed. Eligible individuals willing to participate will be invited for a screening visit. After providing informed consent, individuals will undergo baseline assessment to confirm definitive eligibility for inclusion. A participant must meet all the following inclusion criteria:
Diagnosed with prior poliomyelitis (confirmed by signs of residual weakness and atrophy of muscles on neuromuscular examination, and with electromyography); PPS (according to the March of Dimes criteria [31]); CMT (confirmed by DNA testing or polyneuropathy compatible with CMT and positive family history); or other slowly progressive NMD (with no effective drug therapy).Motivated to improve a reduced physical fitness level.Aged ≥18 years.

And not fulfil any of the following exclusion criteria:
Contraindication for physical activity according to the American College of Sports Medicine (ACSM) guidelines [32].Unable to follow verbal or written instructions.Insufficient competence in the Dutch language.Engaged in an exercise programme (planned, structured, and repetitive physical activity performed at sufficient intensity to improve or maintain physical fitness) for a period longer than 4 weeks in the past 6 months.

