### Randomization and blinding

After baseline assessment and study enrolment, participants will be randomized to the intervention or control group. Randomization will be stratified for diagnosis and treatment centre. We aim for equal group sizes of the three different diagnoses. The randomization scheme will be computer-generated in a Castor EDC database (Castor EDC, Amsterdam, The Netherlands), which uses random blocks of sequences with variable block sizes of two and four. The study coordinator, who is not involved in outcome assessments, will perform the randomization. Independent investigators blinded to group allocation will assess outcomes. Participants cannot be blinded for group allocation, but will be instructed not to reveal their group allocation to the investigators. Analyses will be performed blinded for group allocation.

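### The primary T1 ANCOVA leaves out the randomisation factors that the T2 ANCOVA of the same outcome includes; if those factors are prognostic, the primary test is mildly conservative

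*Protocol article*

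**What the plan says.** In the protocol article, Randomization and blinding states: "Randomization will be stratified for diagnosis and treatment centre". The scheme is one "which uses random blocks of sequences with variable block sizes of two and four". The same section implies three diagnosis levels ("We aim for equal group sizes of the three different diagnoses"), and Study population gives the number of sites: "Participants will be recruited from six participating hospitals and rehabilitation centres".

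Statistical analyses then describes two ANCOVAs of change in VO2peak:

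- **T1 (primary):** the comparison is made "between the groups based on ANCOVA, using the baseline value as covariate".
- **T2 (secondary):** the comparison is made "using the baseline value and stratification factors as covariates".

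The article does not explain why the covariates differ, and no other section adds the stratification factors to the T1 model. Sample size reduces the required number for the baseline correlation only.

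**The concern.** The covariate set is written out for both time points, so this is not a detail left open for an analysis plan. As worded, the primary model ignores the factors used to restrict randomisation, while the next model for the same outcome uses them.

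Stratified blocks make the arms more alike on diagnosis and centre than simple randomisation would. The true sampling variance of the treatment effect then excludes most of the variance due to those factors. A model without them still counts that variance as residual error. If the factors are prognostic after baseline is accounted for, the reported standard error exceeds the true one, the confidence interval is wider than it need be, the test rejects less than 5% of the time under the null, and some power is lost.

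**Working it through.** **The plan's own figures.** Inputs from Sample size: difference 2.5 ml/min/kg, SD 4.7, two-sided alpha 0.05, power 90%, r = 0.71, drop-out 15%.

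- Unadjusted n per group: 75 by the normal approximation; 75.25, rounded up to 76, by the t-based solution. The plan states 76.
- ANCOVA correction: 76 × (1 − 0.71²) = 76 × 0.4959 = 37.7, so 38.
- Drop-out: 38 / 0.85 = 44.7, so 45 per group and 90 in total.

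The stated sample size is reproduced.

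**Formulae.** The residual SD after baseline is 4.7 × √(1 − 0.71²) = 3.31. Let R² be the share of this residual variance explained by diagnosis and centre. The documents do not give R²; 0 to 0.30 is assumed. With exact balance and n = 38 per group:

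- SE reported by the baseline-only model: 3.31 × √(2/38) = 0.759
- true SE: 0.759 × √(1 − R²)
- actual alpha: 2 × [1 − Φ(1.96 × reported SE / true SE)]
- power, baseline only: Φ[(2.5 − 1.96 × 0.759) / true SE]
- power, adjusted: Φ[2.5 / true SE − 1.96]

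| R² | Reported SE | True SE | Ratio | Actual alpha | Power, baseline only | Power, adjusted |
|---|---|---|---|---|---|---|
| 0 | 0.759 | 0.759 | 1.00 | 5.0% | 90.9% | 90.9% |
| 0.10 | 0.759 | 0.720 | 1.05 | 3.9% | 92.0% | 93.5% |
| 0.20 | 0.759 | 0.679 | 1.12 | 2.8% | 93.2% | 95.7% |
| 0.30 | 0.759 | 0.635 | 1.20 | 1.9% | 94.4% | 97.6% |

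**Simulation with imperfect balance.** Three diagnoses by six centres give up to 18 strata, or 90 / 18 = 5 participants per stratum on average. Many blocks stay incomplete, and drop-out disturbs balance further, so the analytic table overstates the effect. Simulated trials used 90 randomised, blocks of 2 and 4, 15% random drop-out, strata filled evenly on average, R² split equally between diagnosis and centre, and 4,000 runs per cell. Each cell shows baseline only / with strata:

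| R² | Mean reported SE | Type I error | Power |
|---|---|---|---|
| 0 | 0.761 / 0.772 | 4.9% / 4.6% | 90.0% / 89.0% |
| 0.10 | 0.762 / 0.733 | 4.6% / 5.4% | 90.0% / 91.2% |
| 0.20 | 0.763 / 0.692 | 3.5% / 5.2% | 91.0% / 94.1% |
| 0.30 | 0.763 / 0.647 | 2.9% / 5.1% | 92.1% / 96.8% |

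The Monte Carlo standard error of a 5% rate with 4,000 runs is √(0.05 × 0.95 / 4000) = 0.34 points, so the 4.6% at R² = 0.10 cannot be told apart from 5% in this set alone. In the baseline-only model the reported SE exceeds the empirical SD of the estimate by about 6 to 9% at R² = 0.20 and 12 to 13% at 0.30. Under a true effect of 2.5, mean estimates from both models are 2.48 to 2.50.

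A second set, with 76 analysed, gave power without / with strata of 89.6% / 88.4% at R² = 0, 90.4% / 91.9% at 0.10, 91.1% / 94.3% at 0.20 and 92.1% / 96.4% at 0.30. Baseline-only type I error was 4.2%, 3.8% and 2.4% at 0.10, 0.20 and 0.30.

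A third set, with 8,000 runs per cell, put the break-even near R² = 0.05: power 90.0% / 90.0% with even centre sizes and 90.7% / 90.8% with uneven ones.

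**The case against.** The strongest reply is that nothing in the documents shows diagnosis or centre to be prognostic for change in VO2peak once baseline is known. At R² = 0 the baseline-only model is slightly the better one, by about 1 point of power, and at about 5% the two models tie. The sample size credits only the baseline correlation, which matches the T1 model as written, so no planned power goes missing. The error is in the safe direction and cannot create a false positive. All of this stands. It makes the standard-error claim conditional and the harm modest. It does not explain why two models for one outcome use different covariates.

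A reader might also infer two further things that the documents do not support.

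- **T1 and T2 effects are not comparable, so sustainability cannot be judged.** In a linear ANCOVA, adding covariates that randomisation balances changes precision, not the quantity estimated. Both effects are differences in change in ml/min/kg. Statistical analyses tests each time point separately and plans no formal T1-versus-T2 contrast.
- **The mixed model for secondary outcomes is deficient because it omits diagnosis.** That model already handles centre ("a random effect for treatment centre will be included to account for partial clustering within centres"), and no calculation shows a loss from leaving diagnosis out.

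**Conclusion.** The mismatch between the T1 and T2 covariates is a matter of plain text and holds whatever R² is. Its statistical consequence is conditional on diagnosis or centre being prognostic beyond baseline. Over the assumed range, type I error is about 4% at a 10% share and 2.4 to 3% at 30%. Power forgone is about 1 point at 10%, 3 points at 20% and 4 to 5 points at 30%.

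It would be tempting to call the primary analysis invalid or underpowered. Neither follows. The estimate is unbiased, and the baseline-only model stays within about half a point of 90% power, or above it, in every scenario. These figures use the 2.5 ml/min/kg set for T2. Sample size expects a somewhat larger change at T1, which would raise power under both models and narrow the gap.

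This is a cheap improvement, not a flaw that threatens the trial's conclusion.

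**What to change.** Specify the primary analysis as an ANCOVA of change in VO2peak from T0 to T1 with treatment group, baseline VO2peak, diagnosis and treatment centre, the two factors entered as main effects, matching the T2 model. If the sponsor prefers baseline only at T1, the reason for the difference should be stated. Either choice should be recorded before group allocation is unblinded, so that only one model can supply the primary p-value.

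The cost is wording. Diagnosis uses 3 − 1 = 2 degrees of freedom. Centre uses 5 with six levels, or 4 if the one organisation listed with two locations is a single level. That is six or seven out of 76 − 3 = 73 with 76 analysed. Both factors are known at randomisation. The downside is about 1 point of power if the strata prove uninformative.

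### Interpolating a missed T1 value from T0 and T2 assumes a trajectory the plan does not expect and pulls the primary VO2peak effect modestly toward zero

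*Protocol article*

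**What the plan says.** The protocol article defines the primary analysis under Statistical analyses: "The primary outcome analysis compares the change from baseline to T1 (directly post-intervention", by ANCOVA on VO2peak with the baseline value as covariate, on all randomised participants. The next sentence is the missing-data rule: "Missing data will be imputed, first by interpolation if possible, and otherwise by multiple imputation". Interpolation thus takes precedence wherever it can be done, and multiple imputation is the fallback. The same section fixes the visit times as the "6-, 12- and 18-month follow-up assessments (i.e. T1, T2 and T3 respectively".

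The Sample size section describes the expected course: "Because the expected change in VO_2peak_ is somewhat larger at T1", the calculation was based on the change to T2. Its inputs begin "Based on an effect size of 2.5 ml/min/kg, 1:1 group allocation, standard deviation of 4.7 ml/min/kg". The section on withdrawal says that people who stop the intervention are still asked to attend the measurements.

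**The concern.** T1 lies midway in time between T0 and T2. A straight line between those two visits gives a T1 value with half of the T2 change. That is right on average only if the benefit builds up steadily to 12 months. The plan expects the reverse: most of the gain by the end of the six-month programme and a somewhat smaller gain at 12 months. For this pattern of missingness, the first-line rule for the primary endpoint therefore contradicts the plan's own picture of the treatment effect.

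The pattern can arise, because participants who stop the intervention are still invited to later visits. It may also be unequal between arms, since only one arm has a programme to stop. At stake is an understated primary effect in a trial meant to inform exercise guidelines.

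**Working it through.** **Inputs from the article.** T1, T2 and T3 at 6, 12 and 18 months; between-group effect at T2 of 2.5 ml/min/kg; SD 4.7; baseline to follow-up correlation r = 0.71; 45 per arm; maximal drop-out 15%; two-sided alpha 0.05; power 90%.

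**Assumptions, not in the article.** Interpolation is linear in time. The T1 effect is at least 2.5; the article says only that the T1 change is somewhat larger than at T2. The control mean does not change. The interpolated share f takes the values 5%, 10% and 15%. In the simulation, T1 is missing completely at random.

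**The plan's own figure.** Two means, difference 2.5, SD 4.7: 75 per group by the normal formula, 75.2 (rounded up to 76) by the t version. Then 76 × (1 − 0.71²) = 37.7, so 38; and 38 / 0.85 = 44.7, so 45 per group. The stated sample size reproduces.

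**Value assigned by the rule.** With T2 present, T1 = (T0 + T2)/2, so the imputed change is 0.5 × (T2 − T0) and carries an expected effect of 0.5 × 2.5 = 1.25. If only T3 is available, the weight is 6/18, one third of the T0-to-T3 change. With T2 present, the rule is unbiased only if the T1 effect is half the T2 effect.

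**Effect on the primary estimate.** Expected estimate = (1 − f) × T1 effect + f × 1.25.

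| f | T1 effect 2.5 | Loss | T1 effect 3.0 (assumed) | Loss |
|---|---|---|---|---|
| 5% | 2.44 | 2.5% | 2.91 | 2.9% |
| 10% | 2.375 | 5.0% | 2.825 | 5.8% |
| 15% | 2.31 | 7.5% | 2.74 | 8.75% |

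With a flat control mean, the share in the intervention arm drives the loss. For the same total number of missed visits, the loss is therefore larger when they fall mainly in that arm.

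**Simulation check.** 45 per arm, 8,000 trials, T1 and T2 effects both 2.5, r = 0.71 between all visits, 7 of 45 per arm missing T1:

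| T1 data used | Estimate | Model SE | Empirical SD | Power | Coverage of true T1 effect |
|---|---|---|---|---|---|
| Complete | 2.52 | 0.70 | 0.70 | 94.6% | 95.1% |
| Interpolated | 2.32 | 0.66 | 0.66 | 93.1% | 94.1% |
| Observed T1 only | 2.51 | 0.76 | 0.76 | 90.3% | 94.9% |

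With no effect at either visit, the rejection rate under interpolation is 4.6%. With a T1 effect of 3.0 and a T2 effect of 2.5, coverage under interpolation is 93.3%. Multiple imputation itself was not simulated.

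**The case against.** **The affected group may be small.** Interpolating T1 needs a later observed visit. Anyone who leaves for good before T1 goes to multiple imputation, and the only missingness figure in the article is total drop-out. With 2 of 45 per arm interpolated, the simulated estimate is 2.44 and coverage 95.2%. This stands, and it keeps the realistic bias small.

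**The error is conservative.** The bias is toward no effect, type I error stays near 5%, and power does not fall below that of an analysis of observed T1 values. This also stands. It limits the severity but does not make the estimate correct.

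**The type of interpolation is not stated.** The exact half depends on a linear rule. Linear in time is the ordinary reading, but it remains an assumption. The order of precedence, by contrast, is fixed in the article and is not a detail left to an analysis plan.

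**Stronger readings that are not supported.** A reader might infer that the confidence interval is too narrow, because the SE of 0.66 is below the 0.70 from complete data and an interpolated value has only a quarter of the residual variance of a real one (2.74 against 10.95). But the right comparison is with the estimator's own sampling spread, and the model SE matches it. The loss of coverage comes from the bias. A reader might also reach a bias of around 15% by setting the T1 effect at 3.0, the T2 effect at 1.5 and missingness at 20% against 5%. That departs from the plan's T2 effect of 2.5 and from a T1 change only somewhat larger, and no figure in the article supports those missingness rates.

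**Conclusion.** The point holds as a bias in the primary estimate, of minor to moderate importance. If interpolation is linear, each participant who misses T1 but attends T2 contributes an expected effect of 1.25 where the plan expects at least 2.5. The resulting loss is about 2.5% at 5% interpolated per arm and 7.5% at 15%, the latter an upper range. It is larger if the T1 effect exceeds 2.5 or if T1 is missed more often in the intervention arm. The size depends on the assumed interpolated shares; the direction follows from the visit times and the plan's expected course. The validity of the test is not threatened.

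**What to change.** Delete the interpolation step for VO2peak and let the multiple imputation already planned handle all missing values. Put T0, T1, T2, T3, randomised group, diagnosis and centre in the imputation model. Impute separately by arm where cell sizes allow, and pool sparse centres: with 45 per arm, several centres and three diagnosis groups, a fully separate model could be unstable. Apply the planned ANCOVA to each imputed set and combine the results. Observed T2 and T3 values still inform a missing T1, without a straight line being forced through them.

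The cost is one changed sentence, slightly more analysis work and a somewhat larger reported SE. No new data or visits are needed. The article reports 40 of 90 participants randomised, so on that status the change could be made before outcomes are compared by group.

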### Withdrawal of participants

Participants can leave the study at any time for any reason if they wish to do so, without any consequences. The investigator can decide to withdraw a participant for urgent medical reasons. Individual participants will not be replaced after withdrawal. Participants who have withdrawn from the intervention will be asked to participate in follow-up measurements.

### Monitoring

Given the low risk for participants, an independent Data Safety and Monitoring Board (DMSB) has not been established. The investigators are responsible for procedures of data monitoring. To facilitate compliance with Good Clinical Practice guidelines, the investigator will permit study-related monitoring, audits, and inspections by authorized organizations.

### Study status

From September 2018 to February 2020, 40 participants were randomized. In the following year we expect to recruit the remaining 50 participants, with the last participant expected to be randomized in March 2021, and finishing the last-follow up measurement in September 2022.

### Patient and public involvement

A multidisciplinary working group consisting of rehabilitation physicians, physical therapists, clinical exercise physiologists and individuals with different NMD were invited to participate in several expert meetings to develop the physical activity program that forms the basis for this I’M FINE project. The expert meetings were used to discuss and adjust the draft versions. Draft versions were developed based on findings of two recent RCTs on aerobic exercise in NMD, experiences of patients and care professionals, and current insights from scientific literature on exercise physiology. A final draft was sent for feedback to the Dutch association for neuromuscular diseases and the Dutch professional associations for rehabilitation medicine and physical therapy. We also incorporated the suggestions from representatives of different diagnoses (CMT and PPS) in the I’M FINE project proposal.

### Public disclosure and publication policy

It is our intention to publish the findings of the study in scientific journals and to present them at scientific meetings. The responsibility for publication and presentation belong to the investigators. Only those investigators making a significant contribution to the study design and/or the collection, analysis or interpretation of the I’M FINE trial data will be eligible for authorship. No restrictions regarding the public disclosure and publication of the research data have been, or will be made, by the funders.

